#### Secondary endpoints

Secondary endpoints of the TRIANGLE trial are as follows:Rate of the following:Microscopically complete margin clearance (> 0.1 cm margin clearance, R0(CRM-))Microscopic margin clearance ≤ 0.1 cm (R0(CRM+))Microscopic margin involvement (R1) resections according to the 8th edition of the UICC TNM classificationRate of the following PD-associated postoperative complications within 90 days after the index operation:Postoperative pancreatic fistula (POPF) as defined by the International Study Group of Pancreatic Surgery (ISGPS) [26]Postpancreatectomy haemorrhage (PPH) as defined by the ISGPS [27]Delayed gastric emptying (DGE) as defined by the ISGPS [28]Bile leakage as defined by the International Study Group of Liver Surgery (ISGLS) [29]Lymphatic fistula as defined by the ISGPS [30]Diarrhoea as graded by the Common Terminology Criteria for Adverse Events (CTCAE) version 5.0 [31]All other postoperative complications graded according to the Dindo-Clavien classification [32] within 90 days. This endpoint complements the PD-associated complications evaluated via the above-mentioned ISGPS endpoints, to assess all remaining postoperative complications to establish a risk-benefit assessment of the two interventions.Overall survival within the study period.Local recurrence within the study period.Quality of life (QoL) according to the European Organisation for Research and Treatment of Cancer (EORTC) QLQ-C30 and PAN26 at discharge and during every follow-up visit compared to baseline.Quality of recovery (QoR) according to the QoR-15 questionnaire on postoperative day 5 compared to baseline.Length of primary hospital stay in days from the day of index operation to the day of discharge.Serious adverse events (SAEs) in both groups .

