### Sample size {14}

The sample size calculation is based on the primary endpoint disease-free survival. The assumptions are based on a median survival time of 14 months in the control group and 21 months in the treatment group resulting in a corresponding hazard ratio of 0.667 assuming exponentially distributed survival times [7, 16, 33]. To detect the assumed difference using a log-rank test at a significance level of 5% (two-sided) with a power of 80%, a total number of 192 events (i.e. recurrence or deaths) are required for the entire trial. It is expected that applying the Cox proportional hazards model, as described below, will lead to an increase in power. With an accrual period of 30 months and a follow-up period of at least 36 months, and assuming an exponentially distributed drop-out rate of 20% (at 66 months), *n* = 270 (135 per group) patients are needed (based on the approximation formula by Schoenfeld). The sample size calculation was done using ADDPLAN 6.1.1.

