## Statistical methods

### Statistical methods for primary and secondary outcomes {20a}

The primary outcome disease-free survival is compared between the groups using a Cox proportional hazards model adjusted for the covariates treatment group, age, neoadjuvant treatment, adjuvant treatment as fixed effects and centre as a random effect. It can be expected that applying the Cox proportional hazards model will lead to an increase in power in comparison with a log-rank test. Confounding by other less important prognostic and predictive factors can be assumed to be controlled by the randomised trial design. The significance level is set to 5% (two-sided). The confirmatory analysis is conducted based on the full analysis set (FAS) according to the ITT principle, i.e. all randomised patients are included and analysed in the treatment group as randomised which reflects a treatment policy approach (according to the ICH E9 (R1) addendum). Death, as an intercurrent event occurring after randomisation, is handled by inclusion into the definition of the primary endpoint which reflects a composite strategy.

All secondary outcomes will be evaluated descriptively, and descriptive *p*-values for the corresponding effects will be reported along with 95% confidence intervals. Continuous variables will be described using a number of missing values, non-missing values, mean, standard deviation, median, Q1, Q3, minimum and maximum. For binary or categorical variables, absolute and relative frequencies will be provided. Thereby, binary and categorical variables will be compared by the chi-squared tests, and continuous variables will be compared with *t*-tests. OS will be analysed analogously to the primary endpoint with a Cox proportional hazards model. QoL will be analysed using linear mixed models with baseline score, age, treatment group and the stratification variables as covariates; centre and time point will be included as random effects. Furthermore, the treatment effect for secondary endpoints will be assessed descriptively within several subgroups to identify potential prognostic and predictive factors. Analyses of secondary endpoints will be based on the ITT population. No imputation of missing values will be conducted in the analyses of secondary endpoints.

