Baseline characteristics will be analysed descriptively with appropriate statistical measures. Further details of the analysis will be specified in the statistical analysis plan (SAP) which will be finalised before database closure. All calculations will be done using SAS version 9.4 or higher.

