### Methods for additional analyses (e.g. subgroup analyses) {20b}

As a sensitivity analysis in the meaning of the ICH E9 addendum, the primary estimand will also be analysed by the unadjusted Cox proportional hazards model. As supplementary analyses, the primary endpoint will also be evaluated based on the per-protocol (PP) population including only those patients without major protocol violations and based on the as-treated set the same way as in the confirmatory analysis. Furthermore, the treatment effect will be assessed descriptively within several subgroups to identify potential prognostic and predictive factors. In addition, further covariables are included and analysed in the primary analysis model in order to identify further possible influencing factors.

For safety analysis, all SAEs will be analysed via descriptive statistical methods. The safety analysis includes calculation of frequencies and rates of complications and serious adverse events together with corresponding 95% confidence intervals. For comparisons of frequencies between the groups, the chi-square test will be used.

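### The chi-squared test named for all categorical secondary endpoints ignores the order of severity grades (Dindo-Clavien, and CTCAE diarrhoea if analysed by grade) and gives no single effect for the promised confidence interval

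*Protocol article*

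**What the plan says.** Section 20a of the protocol article names one test for every categorical secondary endpoint: "Thereby, binary and categorical variables will be compared by the chi-squared tests". Section 20b does the same for complications and serious adverse events: "For comparisons of frequencies between the groups, the chi-square test will be used". Neither section names an ordinal or trend method.

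The list of secondary endpoints contains severity scales. One endpoint is "All other postoperative complications graded according to the Dindo-Clavien classification [32] within 90 days", and its stated purpose is to support a risk-benefit assessment of the two operations. Another is "Diarrhoea as graded by the Common Terminology Criteria for Adverse Events (CTCAE) version 5.0", although this one stands under a heading that speaks of rates. Pancreatic fistula, haemorrhage, delayed gastric emptying, bile leakage and lymphatic fistula, and the three margin categories, are also listed as rates.

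On the status of these analyses section 20a says "All secondary outcomes will be evaluated descriptively", with descriptive p-values for the effects and 95% confidence intervals. Further analysis details are left to the SAP.

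**The concern.** For a severity scale the question has a direction: are complications worse after the TRIANGLE operation? A Pearson chi-squared test on a 2×k table does not use the order of the grades. Its p-value stays the same if the grade labels are shuffled. It spreads its sensitivity over all k−1 ways in which the two grade mixes can differ, so it responds less to the one pattern of interest, a consistent shift towards worse grades.

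The second problem does not depend on power. Section 20a promises a confidence interval for each effect, but a 2×k chi-squared test has no single effect for an interval to describe. For a descriptive harm comparison, the estimate matters more than the p-value.

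At stake is how clearly the harm side of the risk-benefit assessment can be read. The validity of the trial and its primary conclusion are not affected.

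**Working it through.** **Inputs from the article.** Section 14 states "270 (135 per group) patients are needed". The significance level there is 5% two-sided, and it is used here for the descriptive p-values as well. The Discussion gives diarrhoea as 34.4% after TRIANGLE and 14.4% after conventional surgery in the retrospective comparison.

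**Inputs that are assumed.** The article gives no distribution over grades and no expected severity shift. All grade mixes and odds ratios below are assumptions, except the diarrhoea odds ratio in step 4.

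**Step 1: the plan's own figure.** The only power statement concerns disease-free survival. Schoenfeld's formula gives 4 × (1.960 + 0.842)² / (ln 0.667)² = 4 × 7.85 / 0.164 ≈ 191.4, rounded up to 192 events, as stated. There is no stated power for any complication endpoint to reproduce.

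**Step 2: analytic comparison.** Take a shift for which a 1-df test has 80% power. Its noncentrality is λ = (1.960 + 0.842)² = 7.85. Power on d degrees of freedom is P(χ²_d(λ) > χ²_d,0.95).

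| Ordered levels | df | Power | Loss (points) |
|---|---|---|---|
| 2 (binary rate) | 1 | 80% | 0 |
| 3 | 2 | 71% | 9 |
| 4 | 3 | 65% | 16 |
| 6 | 5 | 56% | 25 |
| 8 | 7 | 49% | 31 |

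**Step 3: simulation.** 20,000 trials with 135 patients per arm. If c_j is the control probability of grade j or lower, the TRIANGLE probability is c_j / [c_j + OR × (1 − c_j)]. Pearson's chi-squared (df = non-empty grades − 1) is compared with the tie-corrected Wilcoxon test.

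Control mixes:
- Dindo-Clavien, 8 levels (none, I, II, IIIa, IIIb, IVa, IVb, V): 0.40, 0.15, 0.20, 0.10, 0.07, 0.03, 0.01, 0.04
- Dindo-Clavien, 6 levels: 0.35, 0.12, 0.22, 0.20, 0.07, 0.04
- Dindo-Clavien, 6 levels, mostly complication-free: 0.62, 0.08, 0.12, 0.11, 0.04, 0.03
- CTCAE diarrhoea, grades 0 to 4, with 14.4% affected: 0.856, 0.08, 0.04, 0.02, 0.004
- CTCAE diarrhoea, grades 0 to 4, with 20% affected: 0.80, 0.09, 0.06, 0.045, 0.005

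For the first mix at OR 1.85, for example, the complication-free share falls from 0.40 to 0.40 / (0.40 + 1.85 × 0.60) = 0.265.

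| Endpoint | OR | Chi-squared | Wilcoxon | Loss (points) |
|---|---|---|---|---|
| Dindo-Clavien, 8 levels | 1.85 | 49% | 80% | 31 |
| Dindo-Clavien, 6 levels | 1.5 | 25% | 46% | 21 |
| Dindo-Clavien, 6 levels | 1.75 | 47% | 73% | 26 |
| Dindo-Clavien, 6 levels | 2.0 | 68% | 89% | 21 |
| Dindo-Clavien, 6 levels, 62% none | 1.75 | 41% | 67% | 26 |
| CTCAE diarrhoea, 14.4% affected | 1.5 | 12% | 24% | 11 |
| CTCAE diarrhoea, 14.4% affected | 2.0 | 38% | 61% | 23 |
| CTCAE diarrhoea, 20% affected | 2.1 | 56% | 78% | 22 |

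Over odds ratios 1.5 to 2.0 the loss is 19 to 26 points for six Dindo-Clavien levels, 25 to 33 for eight, and 11 to 23 for diarrhoea. With no difference between arms, both tests reject in at most about 5% of trials. The chi-squared test is somewhat conservative when some grades are rare.

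**Step 4: the documented effect.** The reported diarrhoea rates give an odds ratio of (0.344/0.656) / (0.144/0.856) = 0.524/0.168 = 3.12. Over all grades at about this odds ratio, power is 90% for chi-squared and 98% for Wilcoxon, a loss of about 8 points. As a binary rate, the 2×2 chi-squared test has 97% power. For Dindo-Clavien at OR 3.1 the loss is only 1 to 2 points.

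**Step 5: where the order does not help.** If the difference is not monotone, chi-squared is the stronger test. With the 6-level control mix and a TRIANGLE mix of 0.45, 0.06, 0.12, 0.20, 0.10, 0.07 (more patients without complications and more with severe ones), chi-squared has 70% power and Wilcoxon 6%.

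**The case against.** The strongest case on the other side has four parts.

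1. **Most of the listed complications, and the margin categories, are rates.** Two rates form a 2×2 table, where chi-squared has one degree of freedom and loses nothing. This stands, and it limits the point to Dindo-Clavien and to diarrhoea if it is analysed by grade. Reducing diarrhoea to any versus none would cost almost no power (77% against 78% for the rank test at OR 2.1 with 20% of controls affected), but it would drop severity for the harm the article itself stresses.

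2. **The endpoints are descriptive and carry no power target.** This stands: no stated operating characteristic is breached. A descriptive analysis still needs an interpretable estimate.

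3. **Direction would be visible anyway from frequencies by arm and rates with confidence intervals.** This also stands, so a result could be read as better or worse by eye. The named test still does not measure that direction or summarise it in one estimate.

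4. **Grade handling belongs in the SAP.** In part. The SAP, which is not shown, may add an ordinal analysis. But the article does not leave the test open. It names one for all categorical variables, and a SAP that follows it would carry it over.

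A reader might infer more: that 20 to 30 points are lost on every graded endpoint, or that a real increase in harm would often be missed. The documents do not support this. They give no grade mix or severity shift, they list most of these endpoints as rates, and at the one complication effect they report the loss is small. Nor do the two tests have different null hypotheses. Both test equal grade distributions and differ only in the alternatives to which they are sensitive.

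**Conclusion.** The point holds in a limited form. The test named in section 20a ignores the order of the Dindo-Clavien grades, and of the CTCAE diarrhoea grades if these are analysed as grades. It also supplies no single effect for the promised confidence interval. That second part needs no assumption.

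The loss of sensitivity, roughly 20 to 33 points for a full Dindo-Clavien table and 11 to 23 points for CTCAE diarrhoea, rests on assumed grade mixes, 135 patients per arm and a moderate proportional-odds shift. It shrinks with fewer levels and with large shifts, vanishes for binary rates, and reverses for non-monotone differences. This is an improvement to descriptive secondary analyses. It does not affect the confirmatory analysis or the sample size.

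**What to change.** In section 20a, and correspondingly in the SAP, state:

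*Endpoints recorded as ordered grades (Dindo-Clavien, CTCAE diarrhoea, and any ISGPS/ISGLS or margin variable analysed over more than two ordered levels) will be compared with a Wilcoxon rank-sum test or a proportional-odds model. The common odds ratio, or a rank-based effect measure, will be reported with its 95% confidence interval. Frequencies by grade and arm will be tabulated. Chi-squared tests are used for binary rates and unordered variables.*

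The SAP should choose between the two methods and say which endpoints are analysed as rates and which over grades. Diarrhoea needs this most, because it is graded but listed under rates.

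The cost is one sentence and a standard SAS procedure, with no new data. The article says the SAP is to be finalised before database closure, so the change can be made there. The downside is that the summary odds ratio relies on proportional odds, and a non-monotone difference would be seen only in the table by grade, which is why that table must stay.

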### Recruitment {15}

In order to recruit the necessary number of patients, at least seven pancreatic cancer centres will participate in this trial. All participating trial sites will be high-volume centres with broad expertise in pancreatic surgery and have the necessary expertise, equipment and personnel to perform this trial. Most of the centres are part of the CHIR-Net.

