### Assignment of interventions: allocation

#### Sequence generation {16a}

To ensure an equal distribution of patient characteristics and confounders between the two groups, a randomisation tool will be used. Randomisation will be performed at the patient level with a centralised online randomisation system (www.randomizer.at). The online randomisation procedure provides information regarding the group allocation and a randomisation number. The randomisation sequence is computer-generated and will be stratified by centre and presence/absence of neoadjuvant treatment. Block randomisation will be performed. The randomisation procedure will be performed intraoperatively (after surgical exploration) after the fulfilment of all intraoperative inclusion criteria.

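### QoR-15 is assigned an unadjusted t-test although its baseline is collected; ANCOVA would be more precise at no cost, with a smaller gain from adjusting the complication and margin comparisons

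*Protocol article*

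**What the plan says.** The section on statistical methods for primary and secondary outcomes {20a} sets a default for secondary endpoints: "binary and categorical variables will be compared by the chi-squared tests, and continuous variables will be compared with" *t*-tests. Two secondary endpoints get their own model. Overall survival follows the primary Cox model, and "QoL will be analysed using linear mixed models with baseline score, age, treatment group and the stratification variables as covariates", with centre and time point as random effects.

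QoR-15 gets no model. The list of secondary endpoints defines it as "Quality of recovery (QoR) according to the QoR-15 questionnaire on postoperative day 5 compared to baseline", and Table 2 schedules it at screening and on postoperative day 5. It is listed separately from quality of life, which is defined through the EORTC QLQ-C30 and PAN26. The postoperative complications and the margin categories also have no model, so the chi-squared rule applies to them.

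Randomisation "will be stratified by centre and presence/absence of neoadjuvant treatment" (sequence generation {16a}). Neither factor enters the *t*-tests or chi-squared tests. The status of these analyses is clear: "All secondary outcomes will be evaluated descriptively, and descriptive" *p*-values are reported with 95% confidence intervals.

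**The concern.** One paragraph of the plan treats two patient-reported scores differently. Quality of life is adjusted for its baseline and for the randomisation factors. QoR-15 also has a baseline and comes from the same stratified allocation, but it gets a two-sample *t*-test. The sponsor accepts the general argument elsewhere: both the sample size section and {20a} expect the covariate-adjusted Cox model to gain power over the log-rank test.

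What is at stake is the width of the intervals. The article presents morbidity and patient-reported outcomes as the evidence for a risk-benefit assessment that is now lacking. These endpoints are reported descriptively, so the estimate and its confidence interval are the main product. Precision given away there cannot be recovered from the 270 patients, whereas the baseline score costs nothing extra to use.

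**Working it through.** **The plan's own figures.** No figure is stated for the secondary comparisons. The only stated calculation is for the primary endpoint, "median survival time of 14 months in the control group and 21 months in the treatment group". With Schoenfeld's formula, two-sided 5% and 80% power, events = 4(1.960 + 0.842)² / ln(0.667)² = 31.4 / 0.164, which rounds up to the stated 192. Dividing 192 by the mean event probability with 36 months of follow-up per patient (0.729, exponential drop-out of 20% at 66 months) gives 263, within 3% of the stated 270. If all patients were followed to month 66, the result would be 236. Neither figure uses the secondary analyses, so only the 135 per group is carried forward.

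**QoR-15.** Inputs: 135 per group (sample size section), and a correlation ρ between baseline and day 5. The documents give no ρ, so it is assumed. Equal standard deviations at both times are assumed for the change score. Relative to a *t*-test on the day-5 score:

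- change-score *t*-test: variance ratio 2(1 − ρ)
- ANCOVA: variance ratio 1 − ρ²
- hence ANCOVA against change score: (1 − ρ²) / [2(1 − ρ)] = (1 + ρ)/2

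For power, take the effect that a day-5 *t*-test detects with 80% power: d = 2.802 × √(2/135) = 0.341 standard deviations.

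| ρ (assumed) | ANCOVA / day-5 variance | ANCOVA / change variance | Power: day-5, change, ANCOVA |
|---|---|---|---|
| 0.2 | 0.96 | 0.60 | 80%, 60%, 82% |
| 0.3 | 0.91 | 0.65 | 80%, 66%, 84% |
| 0.5 | 0.75 | 0.75 | 80%, 80%, 90% |
| 0.7 | 0.51 | 0.85 | 80%, 95%, 98% |

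For ρ of 0.3 to 0.5 the variance falls by 9–25% against the day-5 test and by 25–35% against the change score. In interval width this is √0.91 = 0.95 to √0.75 = 0.87 of the day-5 interval, and √0.65 = 0.81 to √0.75 = 0.87 of the change-score interval. ANCOVA is the most precise of the three for every ρ between 0 and 1. Which *t*-test comes second depends on whether ρ is above or below 0.5, so the unstated choice between them also matters.

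**Binary endpoints.** When allocation is stratified but the test ignores the strata, the variance used is too large by the between-stratum part. Its share is w(1 − w)(p₁ − p₂)² / [p(1 − p)], where w is the proportion with neoadjuvant treatment and p₁, p₂ are the stratum rates. The documents give neither, so a 40:60 split and an overall rate of 35% are assumed; w(1 − w) = 0.24 and p(1 − p) = 0.2275.

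- 10-point difference: 0.24 × 0.01 / 0.2275 = 1.1%; standard error too large by 1/√0.989 − 1 = 0.5%; true alpha about 4.9%.
- 25-point difference (20% against 45%): 0.24 × 0.0625 / 0.2275 = 6.6%; standard error too large by 1/√0.934 − 1 = 3.5%; true alpha about 4.3%.

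A second check uses the preliminary rates in the article's discussion, with an assumed standard deviation of risk between strata of 0.05, 0.10 and 0.15; the larger values allow for centre differences as well. Power at 135 per group:

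| Endpoint | Unadjusted | Stratified (0.05, 0.10, 0.15) |
|---|---|---|
| R1 margin, 42.9% vs 31.4% | 49.8% | 50.2%, 51.6%, 53.9% |
| Diarrhoea, 14.4% vs 34.4% | 97.2% | 97.4%, 97.9%, 98.6% |

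True alpha of the plain test is then about 0.049, 0.044–0.045 and 0.037–0.039: conservative throughout, and by little unless the strata differ strongly.

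**The case against.** The strongest reply concerns the baseline score. A reader might infer from the *t*-test rule that the plan discards baseline QoR-15. The documents do not support that: the endpoint is defined in comparison with baseline, so a *t*-test on the change score is a natural reading, and it does use the baseline. This stands. What remains is that the text leaves the choice open and that ANCOVA is more precise under either reading.

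A reader might also infer that the complication and margin comparisons are unsound. They are not. Both QoR-15 tests are unbiased under randomisation, and the chi-squared test errs on the conservative side. The loss is small unless rates differ sharply by stratum, and the documents report no such difference. Diarrhoea, the harm that the article singles out, is detected with about 97% power either way if the preliminary rates hold.

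Stratifying the binary endpoints also has a practical cost. With "at least seven pancreatic cancer centres will participate in this trial", crossing centre with neoadjuvant status gives 14 or more strata. On average that is 270/14, about 19 patients or fewer per stratum and fewer than 10 per group. For uncommon complications many strata would be empty of events. Logistic regression avoids this but estimates a conditional odds ratio, which has to be standardised to give a risk difference. Both points stand and shape the recommendation.

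Finally, further detail is deferred to a statistical analysis plan that is not shown. It may settle whether day-5 or change scores are compared. But the *t*-test is a choice the article states, and an analysis plan that follows it would inherit that choice.

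**Conclusion.** The point holds for QoR-15 as a free gain in precision. At an assumed ρ of 0.3 to 0.5, ANCOVA lowers the variance by 9–25% against a day-5 *t*-test or 25–35% against a change-score *t*-test. Over ρ of 0.2 to 0.7 the ranges are 4–49% and 15–40%. These sizes rest on assumed correlations and, for the change score, on equal standard deviations; the ordering does not depend on the particular ρ assumed. The number analysed may be somewhat below 135 per group, because the day-5 visit is skipped for patients already discharged.

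For complications and margins the gain is minor: an excess in standard error of about 0.5% to 3.5% for assumed 10- to 25-point differences by neoadjuvant status. It would not merit a change by itself.

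It would be wrong to conclude that type I error is inflated, that any estimate is biased, or that the confirmatory result is at risk. These are descriptive secondary analyses, and the primary conclusion and the sample size of 270 do not depend on them.

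**What to change.** State that QoR-15 on postoperative day 5 will be analysed by ANCOVA, with treatment group, baseline QoR-15 and neoadjuvant treatment as fixed effects and centre as a random effect, and report the adjusted mean difference with its 95% confidence interval. This brings it into line with the quality-of-life model (age could be added to match it fully) and removes the ambiguity between day-5 and change scores.

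As a lower-priority companion, adjust the complication and margin comparisons for neoadjuvant treatment and centre, with centre as a random effect or pooled to avoid sparse strata. Report a standardised or stratified risk difference with 95% confidence interval beside the crude frequencies.

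The cost is analysis wording only. Every variable is already collected, no patient or visit is added, and the statistical analysis plan is due to be finalised before database closure.

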### Participant timeline {13}

Patients scheduled for elective PD will be screened preoperatively (visit 1). After the patient has given informed consent, the inclusion and exclusion criteria are assessed during the screening visit. Patients fulfilling all the inclusion criteria and none of the exclusion criteria and who consent to take part in the trial are randomised during surgery (visit 2; surgery and randomisation) after the surgeon has obtained certainty that both interventions can be performed in the patient. The results of the pathologic work-up (secondary endpoint) will also be recorded in the eCRF section of visit 2. Patients are planned for follow-up visits on postoperative days 5, 10–12 and 90 (visits 3, 4 and 6) for the evaluation of primary and secondary endpoints. Visit 5 will be performed at discharge. If discharge occurs before visit 3 or 4, the respective postoperative visits (3 or 4) can be omitted. In addition, 6, 12, 18, 24, 30 and 36 months (visits 7–12) after surgery, patients are planned for follow-up visits to evaluate primary and secondary outcome parameters (Fig. 1 and Table 2).

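### The quality-of-life mixed model, as written, has no patient term for repeated scores, so its intervals and descriptive p-values for treatment would be too narrow and too small

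*Protocol article*

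**What the plan says.** The section on statistical methods for primary and secondary outcomes ({20a}) names the terms of the QoL model: "QoL will be analysed using linear mixed models with baseline score, age, treatment group and the stratification variables as covariates". The same sentence closes with "the stratification variables as covariates; centre and time point will be included as random effects". Neither there nor elsewhere does the article mention a patient effect, a repeated-measures term or a within-patient covariance for QoL.

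The scores are repeated. The secondary endpoint is QoL on the EORTC QLQ-C30 and PAN26 "at discharge and during every follow-up visit compared to baseline". Table 2 marks QoL at screening, at discharge and at visits 7 to 12. The participant timeline ({13}) places those visits at "6, 12, 18, 24, 30 and 36 months (visits 7–12) after surgery". That gives one baseline score and up to seven later ones. Table 2 does not mark QoL at postoperative day 90; the endpoint wording could be read to add it.

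Randomisation is "stratified by centre and presence/absence of neoadjuvant treatment" ({16a}). The status of the results is also stated: "All secondary outcomes will be evaluated descriptively, and descriptive *p*-values for the corresponding effects will be reported along with 95% confidence intervals".

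**The concern.** A random centre effect is shared by all patients of a centre. A random time-point effect is shared by everyone seen at that visit. Neither makes two scores from the same patient more alike than scores from two different patients. The baseline covariate takes out some of the stable difference between patients, but not all of it. What remains is treated as fresh, independent information at every visit.

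Treatment is a patient-level factor, so the error goes directly into its standard error. The primary model in the same section can do without a patient effect because each patient has one disease-free survival time. QoL has up to seven values per patient, so that reasoning does not carry over.

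At stake are the 95% confidence intervals and descriptive p-values for the treatment effect on the QoL scales. The article's discussion names patient-reported outcomes among the missing data that preclude an informed risk-benefit assessment, and cites earlier data with more diarrhoea after extended surgery. Intervals that are too narrow could make a chance difference look like an effect of the operation, in either direction.

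**Working it through.** **The plan's own figure.** The article gives no standard error, correlation or power for QoL, so there is none to reproduce. Its one computed requirement, 192 events for disease-free survival, reproduces: 4 × (1.960 + 0.842)² / (ln 0.667)² = 31.4 / 0.164 = 191.4, rounded up to 192. Nothing about QoL enters it.

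**Inputs from the article.** 270 patients; up to seven post-baseline scores, at discharge and months 6, 12, 18, 24, 30 and 36; drop-out of 20% at 66 months.

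**Assumed inputs.** Residual within-patient correlation ρ after baseline adjustment, 0.2 to 0.6; median overall survival 24 months, exponential; 85% questionnaire completion.

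**Formulas.** For a patient-level effect with m scores per patient, the design effect is DE = 1 + (m − 1)ρ. True SE / reported SE = √DE. The rejection rate of a nominal 5% test under no effect is 2(1 − Φ(1.96/√DE)).

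**Step 1, upper bound: all seven scores.**

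| ρ | DE | √DE | Rejection under no effect |
|---|---|---|---|
| 0.2 | 2.2 | 1.48 | 19% |
| 0.4 | 3.4 | 1.84 | 29% |
| 0.6 | 4.6 | 2.14 | 36% |

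**Step 2, allow for deaths and missing forms.** The proportions alive at the seven visits, 0.5^(t/24) with discharge at about 0.5 months, are 0.986, 0.841, 0.707, 0.595, 0.500, 0.420 and 0.354. They sum to 4.40, and 4.40 × 0.85 = 3.7 scores per patient. The article's drop-out lowers this slightly; leaving out patients with no score raises it again.

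Patients contribute unequal numbers, and those with many scores weigh more. The m for the formula is therefore Σm²/Σm rather than the plain mean. Drawing visit counts under these assumptions gives about 4.8 with the article's drop-out (5.0 without it). Then:

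- ρ = 0.2: DE = 1 + 3.8 × 0.2 = 1.76, √DE = 1.33, rejection 14%.
- ρ = 0.6: DE = 1 + 3.8 × 0.6 = 3.28, √DE = 1.81, rejection 28%.

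Putting the plain mean of 3.7 in the formula gives a milder 1.24 to 1.62, and 11% to 23%.

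**Step 3, simulation under no treatment effect.** 2,000 trials were run per correlation, with no patient effect. Centre and visit were fitted as fixed effects, as a stand-in for the random ones.

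| ρ | True SE / reported SE | Rejection |
|---|---|---|
| 0.2 | 1.32 | 14.2% |
| 0.3 | 1.50 | 19.9% |
| 0.4 | 1.58 | 21.2% |
| 0.5 | 1.72 | 25.8% |
| 0.6 | 1.80 | 28.0% |

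**Step 4, random centre and time point as the article names them.** At ρ = 0.4, 225 runs, some with convergence warnings, gave 16% rejection. Adding a patient random intercept gave 4.9%. Mean SEs were 0.065 and 0.098, a ratio of 1.51. The Monte Carlo interval for the 16% is 16 ± 4.8 percentage points, about 11% to 21%.

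**Step 5, other assumptions.** A separate simulation (1,500 runs per setting, ρ from 0.2 to 0.7) gave 19% to 41% with all seven scores. With assumed median survival of 21 to 28 months it gave 15% to 34%. A patient random intercept brought rejection back to 4.1% to 6.1% throughout.

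**The case against.** The strongest reply is that the sentence is shorthand. The article defers further analysis details to an SAP that is not shown, and the subject unit and covariance type are often settled there. A random time point may be loose wording for a repeated effect within patient; if so, the intended analysis is sound and only the sentence needs repair. This stands as a possibility, and a reader should not infer that the sponsor has decided to ignore the correlation. But the article does not leave the structure open. It names the random effects, gives time point the same role as centre and mentions no subject. An SAP that follows the sentence inherits the error.

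Second, QoL is secondary and its p-values are descriptive. This stands and limits the seriousness. A reader might infer that the trial's main conclusion is at risk; it is not, because neither the disease-free survival model nor the number of patients depends on this sentence. Descriptive confidence intervals must nevertheless have the right width.

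Third, the size rests on assumed correlation, survival and completion, and most of the simulation used a stand-in for the random effects. This also stands. The direction is firm under the literal reading; 14% to 28% is an illustration over a stated range.

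Fourth, a reader might infer that centre is entered twice, as a stratification covariate and as a random effect. The text does not clearly support that. The primary model in the same section has neoadjuvant treatment fixed and centre random only, and the QoL sentence can be read the same way. The wording merits tidying, but no harm has been shown from it.

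**Conclusion.** The point holds for the QoL model as written: repeated scores from a patient are treated as independent given the covariates, and the precision of the treatment effect is overstated. For a residual within-patient correlation of 0.2 to 0.6, with about 3.7 scores per patient (assumed 24-month median survival and 85% completion), the true standard error is roughly 1.3 to 1.8 times the reported one. Nominal 5% tests reject in roughly 14% to 28% of null cases. Fewer scores or a lower correlation shrink the problem; complete follow-up enlarges it.

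The consequence is confined to secondary, descriptive results. It should be fixed because those results inform the risk-benefit assessment, but it is not a threat to the confirmatory analysis.

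**What to change.** In {20a}, replace the random-effects clause of the QoL sentence with wording such as: *Repeated scores within a patient will be modelled with a patient random intercept or a within-patient covariance structure (for example unstructured). Visit will be a fixed categorical effect. Centre enters once, as a random effect, and neoadjuvant treatment as a fixed effect, as in the primary model.* The SAP should carry the same structure. An unstructured covariance with Kenward-Roger degrees of freedom is one sound choice among several; a patient random intercept also restored the error rate in the checks above.

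If the time-point term was meant as a within-patient effect, the same sentence settles it.

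The cost is one sentence and a line of SAS code, with no extra data or patients. The QoL intervals will be wider, which is their correct width.
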